# Electronic health record nested pragmatic randomized controlled trial of a reminder system for serum lithium level monitoring in patients with mood disorder: KONOTORI study protocol

**DOI:** 10.1186/s13063-019-3847-9

**Published:** 2019-12-11

**Keywords:** Electronic health record, Pragmatic trial, Mood disorder, Lithium carbonate, Randomized controlled trial

## Abstract

**Background:**

The weaknesses of classical explanatory randomized controlled trials (RCTs) include limited generalizability, high cost, and time burden. Pragmatic RCTs nested within electronic health records (EHRs) can be useful to overcome such limitations. Serum lithium monitoring has often been underutilized in real-world practice in Japan. This trial aims to evaluate the effectiveness of the EHR-nested reminder system for serum lithium level monitoring in the maintenance of therapeutic lithium concentration and in the improvement of the quality of care for patients on lithium maintenance therapy.

**Methods:**

The Kyoto Toyooka nested controlled trial of reminders (KONOTORI trial) is an EHR-nested, parallel-group, superiority, stratified, permuted block-randomized controlled trial. Screening, random allocation, reminder output, and outcome collection will be conducted automatically by the EHR-nested trial program. Patients with a mood disorder taking lithium carbonate for maintenance therapy will be randomly allocated to the two-step reminder system for serum lithium monitoring or to usual care. The primary outcome is the achievement of therapeutic serum lithium concentration between 0.4 and 1.0 mEq/L at 18 months after informed consent.

**Discussion:**

The KONOTORI trial uses EHRs to enable the efficient conduct of a pragmatic trial of the reminder system for lithium monitoring. This may contribute to improved quality of care for patients on lithium maintenance therapy.

**Trial registration:**

University Hospital Medical Information Network (UMIN) Clinical Trials Registry, UMIN000033633. Registered on 3 July 2018.

## Background

### Background and rationale

#### Limitations of classical “explanatory” randomized control trials and the potential of the electronic health record nested randomized control trial

Randomized control trials (RCTs) have been the gold standard to evaluate the benefits and harms of interventions. However, problems with the classical “explanatory” RCTs have been reported [1]. First, the generalizability of the results of explanatory RCTs is usually limited because only ideal patients are included owing to the RCT stringent eligibility criteria [2]. In addition, the recruitment of adequate numbers of participants is becoming increasingly difficult because of the expense and the time burden on clinicians [3].

Pragmatic trials have been proposed to increase the generalizability by conducting RCTs under routine clinical practice conditions rather than in specialized environments [4]. For the past few decades, electronic health records (EHRs) have been used widely for observational pharmacoepidemiology and clinical studies [5, 6]. Recently, some pragmatic RCTs, which are called EHR-nested RCTs, have used EHRs to assess the effectiveness of various interventions [7–11]. The EHR-nested RCT aims to increase the feasibility of RCTs by using an EHR to reduce trial costs, time burden, and human resources [12, 13]. The use of EHRs may allow pragmatic RCTs to be conducted in routine care settings. In addition, EHR-nested systems were shown to increase the referral and recruitment of participants in some studies [14, 15]. Although the benefits of EHR-nested RCTs have continued to emerge, most of these studies have been conducted in the USA and UK, and the feasibility of EHR-nested RCTs in other clinical environments is still uncertain [3, 9, 11, 16].

#### Mood disorder and lithium carbonate

The World Health Organization has reported that major depression is the third most common cause of years lost due to disability and the 16th most common cause of disability-adjusted life years [17]. Behind alcohol abuse, major depressive disorder is the second most frequent psychiatric disorder in Japan, with a lifetime prevalence of 5.7%. Bipolar disorder is rare compared with major depressive disorder; the lifetime prevalence of bipolar I disorder is 0.4% [18].

Lithium carbonate is a mood stabilizer used for maintenance treatment of bipolar disorder and recurrent unipolar depression [19, 20]. Owing to its narrow therapeutic range, regular serum lithium monitoring is strongly recommended, every week in the acute phase and every 3 months during the subsequent maintenance phase [21–23]. However, the rates of monitoring vary greatly in different countries, from 30% to 65% [24, 25]. In 2012, the Pharmaceutical and Medical Devices Agency (PMDA) in Japan warned against poor utilization of serum lithium monitoring, because 52% of patients who were prescribed lithium carbonate had not had their serum lithium monitored [26]. However, despite the regulatory alerts, a recent study revealed that serum lithium was monitored at least once a year in only 15% of patients [27]. After a substantial literature search, we identified no study of monitoring to improve the adherence of lithium monitoring.

### Objective

The purpose of the Kyoto Toyooka nested controlled trial of reminders (KONOTORI trial) is to examine whether the EHR-nested reminder system for serum lithium monitoring is feasible in routine clinical practice in Japan, and whether it can help to achieve therapeutic serum lithium concentration and improve outcomes for patients on lithium maintenance therapy.

## Methods/design

### Trial design

The trial is an open-label, parallel-group, single-center, superiority RCT to evaluate the effectiveness of an EHR-nested reminder system for serum lithium monitoring. The trial program in the EHR system automatically prompts for eligibility screening, conducts the random allocation, outputs reminders, and collects outcomes.

### Participants, interventions, and outcomes

#### Study setting

The trial is being conducted at the outpatient clinic of a psychiatry department at Toyooka hospital, a 518-bed tertiary care community hospital in Toyooka City, Hyogo, Japan, which has a population of 85,000. All physicians participating in the trial are psychiatrists. The trial program covers the entire EHR system in Toyooka Hospital but the reminder itself works only at the department of psychiatry.

### Participants

#### Eligibility criteria

Participants will be recruited in accordance with the eligibility criteria described below.

##### Inclusion criteria

The participant must fulfill all the following:
Age ≥ 18 years on the day of informed consentHas recurrent major depression, bipolar I disorder, or bipolar II disorder according to the *Diagnostic and statistical manual of mental disorders, 5th edition* (DSM-5)Has been taking lithium carbonate for 6 months or longerHas been judged by the treating physician to need a prescription of lithium carbonate for the next 18 months

##### Exclusion criteria

The participant must not meet any of the following criteria:
Prescribed lithium carbonate for an indication other than mood disordersA primary diagnosis of schizophreniaJudged by the treating physician to have an imminent high risk of suicideSuspected to have lithium intoxicationWomen who are pregnant or breastfeedingCohabiting family members of study staff personnelInability to understand written JapaneseContraindications to lithium carbonateParticipating in another clinical trialCurrently hospitalizedTerminal physical diseaseNo serum lithium concentration available within 7 days of informed consentNo appointment between 4 and 8 months after informed consentWritten informed consent is unavailableJudged by the treating physician as inappropriate for participation

(criteria 12 and 13 may be confirmed after informed consent, but before randomization)

### Interventions

The trial program outputs two-step reminders of serum lithium monitoring to the treating physician as specified by the algorithm. When a participant in the intervention group visits the outpatient clinic between 4 and 8 months after the last lithium monitoring or at the study registration, reminder A will be sent to the treating physician. If the participant visits within 8 months after reminder A, reminder B will be sent. After reminder B has been sent and the participant visits the clinic thereafter, reminder A will be sent another time. No reminder will be sent if the participant receives lithium monitoring within 4 months, visits the outpatient clinic after 8 months or more, or if the participant is in the control group.

We anticipate that the two-step reminders will improve both the physician’s awareness and the participant’s adherence:
Reminder A

The text of reminder A is as follows: “Please notify the participant of the need for a blood test for serum lithium level at the next outpatient visit. If the next visit will be 8 months or further from the previous blood test, please notify the participant of the need to conduct a blood test today. The participant and the treating physician can decide whether to conduct the blood test.”
Reminder B

The text of reminder B is as follows: “Please notify the participant the need for a blood test for serum lithium level today. The participant and the treating physician can decide whether to conduct the blood test.”

#### Control

Participants in the control group receive usual care without reminders.

#### Concurrent treatment and concerns about contamination

There are no restrictions on concurrent treatments in the trial.

### Outcomes

At the first scheduled visit, between 18 and 24 months after informed consent, the program will output a reminder for the final evaluation. The treating physician will conduct a blood test within 7 days of the visit.

#### Primary outcome

The primary outcome is the achievement of therapeutic serum lithium concentration between 0.4 and 1.0 mEq/L at 18 months after informed consent. If a participant withdraws during the follow-up period or the result of the final blood test is not available, he/she will be regarded as not having achieved the primary outcome, because unavailability for the final serum lithium measurement strongly implicates that the patients is not adherent. However, the validity of this assumption will be tested in a sensitivity analysis using multiple imputation (see “Statistical analyses”).

#### Secondary outcomes

The secondary outcomes are as follows:
The number of blood tests for serum lithium concentration in the 18 months period after the date of informed consent.Exacerbation of major depression or bipolar disorder in the 18-month period from the date of informed consent, defined by at least one of the following: hospitalization; increase in lithium dose; addition of antipsychotic drugs or mood stabilizer (valproic acid, carbamazepine, lamotrigine); or addition of or increase in use of antidepressants.Proportion of days covered (PDC) of lithium carbonate prescription during the 18 months after informed consent [28].Thyroid-stimulating hormone (TSH) ≥ 1.0 μIU/mL after 18 months.Estimated glomerular filtration rate (eGFR) < 60 mL/min per 1.73 m^2^ after 18 months.

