#### Eligibility check and registration

Primary Care Evaluation of Mental Disorders (PRIME-MD) is a semi-structured diagnostic tool to assist primary care physicians in the diagnosis of common mental disorders based on the DSM-5 [29]. The treating physician conducts the PRIME-MD and confirms the diagnosis of depression, bipolar I, or bipolar II. If the candidate meets the eligibility criteria and written informed consent is obtained, the treating physician registers the participant through the EHR. If the candidate is not eligible, refuses participation, or withdraws after participation, the treating physician enters the status through EHR. The treating physician will conduct a baseline blood test within 7 days of the patient giving informed consent. If the candidate does not receive the baseline blood test or a measurement of serum lithium is not available within 7 days, he/she will be excluded from the study.

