### Assignment of intervention

#### Randomization

The participants will be stratified into nine strata in accordance with the following two conditions in EHR, and automatically randomized by the trial program at their first scheduled visit between 4 and 8 months after informed consent, using permuted block randomization [30].
Diagnosis based on PRIME-MD (major depression, bipolar I disorder, or bipolar II disorder)Serum lithium (between 0.4 mEq/L and 1.0 mEq/L; < 0.4 mEq/L; or > 1.0 mEq/L)

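### Three of the five secondary outcomes are counted from informed consent, 4 to 8 months before randomization, so 22–44% of each 18-month window cannot differ by arm

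*Protocol article*

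**What the plan says.** Under Secondary outcomes, the protocol article starts three outcomes at consent:

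- "The number of blood tests for serum lithium concentration in the 18 months period after the date of informed consent"
- "Exacerbation of major depression or bipolar disorder in the 18-month period from the date of informed consent", met by at least one of several qualifying events
- "Proportion of days covered (PDC) of lithium carbonate prescription during the 18 months after informed consent"

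The other two secondary outcomes, TSH and eGFR, are threshold results from a single measurement after 18 months.

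Under Randomization, participants are "automatically randomized by the trial program at their first scheduled visit between 4 and 8 months after informed consent". The exclusion criteria agree with that order, since "criteria 12 and 13 may be confirmed after informed consent, but before randomization". One of those two criteria is the lack of an appointment in the 4-to-8-month interval.

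Eligibility check and registration adds a test common to both arms: "The treating physician will conduct a baseline blood test within 7 days of the patient giving informed consent". Under Interventions, reminders go only to the intervention group, and none is sent when lithium was tested within the preceding 4 months.

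**The concern.** An arm can affect only what happens after allocation. Tests, exacerbations and covered days from the first 4 to 8 months have the same expected value in both arms, yet they enter the comparison with the same weight as later time.

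Exacerbation is the most exposed of the three because it is a yes/no outcome. A participant who has a qualifying event before randomization is already a case, whichever arm follows, and can no longer contribute information on the reminder. The definition includes an increase in lithium dose. Screening selects people with no lithium result in the previous 4 months, who are then tested at baseline, so a dose change prompted by that result would be an event before allocation.

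At stake are attenuated estimates for three exploratory outcomes. A reader could also take them for the effects of 18 months of reminders, when the intervention can have acted for only 10 to 14 months by month 18.

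**Working it through.** The document gives no figure for the pre-randomization share, so there is none to reproduce. The 18-month window comes from Secondary outcomes, and the time to randomization, t = 4 to 8 months, from Randomization. All effect sizes and event rates below are assumptions for illustration.

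**Share of the window before randomization**, f = t/18:
- t = 4: 4/18 = 22.2%, leaving 14 months
- t = 8: 8/18 = 44.4%, leaving 10 months

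**PDC.** The window value is f × (PDC before) + (1 − f) × (PDC after), so a true difference after randomization is multiplied by 1 − f. For an assumed 10 points:
- t = 4: 10 × 14/18 = 7.8 points
- t = 8: 10 × 10/18 = 5.6 points

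**Number of tests.** With usual-care rate r per month and an assumed doubling after randomization, the observed ratio is [t·r + (18 − t)·2r]/(18r):
- t = 4: (4 + 28)/18 = 1.78
- t = 8: (8 + 20)/18 = 1.56

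The expected difference is (18 − t)·r with or without the earlier months, so it does not shrink. If counts are Poisson (a further assumption), the variance of the difference is proportional to 3(18 − t) from randomization and 3(18 − t) + 2t from consent:
- t = 4: 50 against 42, standard error × √(50/42) = 1.09
- t = 8: 46 against 30, standard error × √(46/30) = 1.24

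**Exacerbation.** Assume a control risk of 30% over 18 months, a constant hazard that earlier events do not change, and a hazard ratio of 0.6 after randomization. Then h = −ln(0.7)/18 = 0.0198 per month.
- From randomization: control risk 1 − exp[−h(18 − t)]; intervention risk 1 − exp[−0.6h(18 − t)]
- From consent: control risk 0.30; intervention risk 1 − exp[−ht − 0.6h(18 − t)]

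| | t = 4 | t = 8 |
|---|---|---|
| From randomization, control / intervention | 24.2% / 15.3% | 18.0% / 11.2% |
| Risk ratio; risk difference | 0.63; 8.9 points | 0.62; 6.8 points |
| From consent, control / intervention | 30.0% / 21.8% | 30.0% / 24.2% |
| Risk ratio; risk difference | 0.73; 8.2 points | 0.81; 5.8 points |
| Control cases with first event before randomization, (1 − exp[−ht])/0.30 | 25% | 49% |

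If the assumed control risk is varied from 20% to 40%, the risk ratio from consent is 0.71–0.74 at t = 4 and 0.80–0.82 at t = 8, so the pattern does not depend on the 30%.

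**The case against.** Several points on the other side stand. The time origin is stated openly. The Statistical analysis section calls the secondary analyses exploratory, and Limitations already concedes too little power for exacerbation. The months before randomization are common to both arms, so they cannot manufacture a benefit. On the difference scale the loss for exacerbation is modest.

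One might also argue about when randomization happens. Footnote a of Table 1 could be read as randomizing once an appointment has been booked. The Randomization section is explicit that it happens at the visit. On the other reading the problem would remain, because the baseline test keeps roughly the first 4 months free of reminders in both arms. The Interventions wording, "visits the outpatient clinic between 4 and 8 months after the last lithium monitoring or at the study registration, reminder A will be sent", does not change this, since a reminder needs an allocation first.

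Three stronger readings are tempting, and the document does not support them:

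- A reader might infer that every secondary outcome, or the primary, is diluted. The primary outcome, TSH and eGFR are single late measurements with no accumulating window.
- A reader might infer that any effect measure shrinks. The expected absolute difference in test counts does not, and the protocol article fixes no ratio measure for that outcome.
- A reader might infer that the baseline test is certainly counted and costs precision. The outcome runs from after the consent date and the test may fall within 7 days of consent, so its inclusion is ambiguous. If counted for everyone, it is a constant of one per participant, which alters neither the difference nor its standard error. It would only lower the ratio: at an assumed one test per year, (1 + 4/12 + 2 × 14/12)/(1 + 18/12) = 1.47 at t = 4, and (1 + 8/12 + 2 × 10/12)/(1 + 18/12) = 1.33 at t = 8.

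**Conclusion.** The point holds for the number of lithium tests, exacerbation and PDC. The share of each window before randomization, 22–44%, follows directly from the protocol article's own timings. No section shown restricts these outcomes to time after randomization, and Limitations does not mention it.

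The PDC difference is attenuated by the same 22–44%. Exacerbation is attenuated on both scales, more visibly on the ratio than on the difference, with sizes that depend on the assumed hazard and effect. For test counts the ratio is attenuated, while the difference keeps its expected value and becomes noisier. The direction is toward no effect throughout. This is a correctable weakness in exploratory outcomes and no threat to the primary comparison.

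**What to change.** Define, or at least analyse, the three outcomes from the date of randomization to 18 months after consent:

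- **Number of tests:** count from randomization with log follow-up time as an offset. This also removes the baseline test and the ambiguity about it.
- **Exacerbation:** first qualifying event after randomization, analysed as time from randomization.
- **PDC:** use days since randomization as the denominator.

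Use the consent-to-randomization values of each outcome as baseline covariates. The consent-based versions can stay as supplementary analyses. State in the report that exposure to the reminder at month 18 is 10–14 months.

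The cost is small. Data collection and management says that the trial program already stores the randomization information, so no new data or visits are needed. Follow-up will vary between participants by up to 4 months, which the offset and the time-to-event analysis handle. The change must be entered in the SAP, which the Statistical analysis section says will be finalized before the last participant's outcomes are registered. If the outcome definitions themselves are changed, it must go through the two-step ethics approval described under Protocol amendments.

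### The exacerbation outcome sets no cause for hospitalization and counts antipsychotics and three mood stabilizers only when added, so it can misclassify participants in both directions

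*Protocol article*

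**What the plan says.** The Secondary outcomes section of the protocol article names the outcome as "Exacerbation of major depression or bipolar disorder in the 18-month period from the date of informed consent". A participant has the event on meeting any one of four components. The first three are given as "defined by at least one of the following: hospitalization; increase in lithium dose; addition of antipsychotic drugs or mood stabilizer (valproic acid, carbamazepine, lamotrigine", with the list of mood stabilizers closing there. The fourth is "addition of or increase in use of antidepressants".

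No section adds a cause, ward or diagnosis to the hospitalization component, and none describes adjudication. The Study setting section describes the site as "a 518-bed tertiary care community hospital in Toyooka City" and adds: "The trial program covers the entire EHR system in Toyooka Hospital". Patients with bipolar I, bipolar II and recurrent major depression are all eligible, and concurrent treatment is unrestricted. Suicide appears only in an exclusion criterion, for imminent high risk.

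**The concern.** A literal application of the list can go wrong in both directions.

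- **Events that are not exacerbations.** An admission for a fracture or pneumonia meets the first component. So does one for lithium intoxication, acute kidney injury or bradycardia, which the section on foreseeable adverse events lists as serious side effects of lithium. A harm of treatment would then be recorded as a mood relapse.
- **Exacerbations that are not events.** Raising an antidepressant counts. Raising an antipsychotic, valproic acid, carbamazepine or lamotrigine does not, and the article gives no reason for the difference.
- **Suicide.** A death with no earlier admission or qualifying drug change is scored as no exacerbation.

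The Objective section includes improving patient outcomes. The Limitations section calls exacerbation a more appropriate primary outcome in principle than serum lithium. This composite is the trial's only measure of mood relapse. Few exacerbations are expected, and the fewer the true events, the more unrelated admissions distort the relative effect.

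**Working it through.** **Step 1: the drug rules side by side (Secondary outcomes).**

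| Drug class | Added | Increased |
|---|---|---|
| Lithium | not applicable: taken for 6 months or longer at entry | event |
| Antidepressants | event | event |
| Antipsychotics | event | no event |
| Valproic acid, carbamazepine, lamotrigine | event | no event |

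An episode is therefore missed only if all of these hold: no admission, no lithium increase, no added antipsychotic or named mood stabilizer, no new or increased antidepressant, and the sole response was to raise an antipsychotic or named mood stabilizer already taken. Unrestricted concurrent treatment makes this possible. The documents do not give the share of participants on such drugs.

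**Step 2: unrelated admissions.** The article gives no exacerbation or admission rate, so there is no figure of its own to reproduce. All inputs here are assumptions: true risk p of 30% (control) and 15% (intervention), and an independent risk h of unrelated admission, equal in both arms.

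Observed risk = 1 − (1 − p)(1 − h)

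| h | Control | Intervention | Risk ratio | Risk difference (points) |
|---|---|---|---|---|
| 0% | 0.300 | 0.150 | 0.50 | 15.0 |
| 5% | 1 − 0.70 × 0.95 = 0.335 | 1 − 0.85 × 0.95 = 0.1925 | 0.57 | 14.25 |
| 10% | 1 − 0.70 × 0.90 = 0.370 | 1 − 0.85 × 0.90 = 0.235 | 0.64 | 13.5 |
| 15% | 1 − 0.70 × 0.85 = 0.405 | 1 − 0.85 × 0.85 = 0.2775 | 0.69 | 12.75 |

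The risk difference is simply 15.0 × (1 − h). With assumed true risks of 20% vs 10%, the risk ratio moves from 0.50 to 0.60, 0.68 and 0.73.

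**Step 3: missed events.** If a share Se of true events is captured equally in both arms and nothing else is wrong, observed risk = Se × p. The risk ratio stays at 0.50. The risk difference falls to 0.9 × 15.0 = 13.5 points at Se 0.9, and to 12.0 at Se 0.8.

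**Step 4: power.** Take 54 per arm, the per-group number in the Sample size calculation section, and a two-sided 5% test at the assumed 30% vs 15%. Power is 46% with perfect classification, and 39%, 33% and 28.5% at h = 5%, 10% and 15%. The outcome is underpowered before any misclassification.

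**The case against.** The strongest reply is that silence is being read as a rule. The outcome is titled as exacerbation of a mood disorder, and nothing says an admission for surgery will be scored. That the trial program spans the whole record system does not show that non-psychiatric admissions enter this outcome. The article may condense a fuller rule, and it defers analysis details to a statistical analysis plan. It is fair to say that the cause is unspecified, not that unrelated admissions are deliberately included. But the article states the rule down to drug names and the difference between adding and raising. As published, the list is closed and nothing narrows it.

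Four stronger readings are tempting, and the documents do not support them:

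- **That mania treated by raising any mood stabilizer is missed.** Lithium is a mood stabilizer, all participants enter on it, and its increase counts. The Limitations section says the hospital is the region's only provider of inpatient psychiatric care, so severe episodes admitted locally should be captured.
- **That suicide passes as a success.** This holds only within this one composite, and only without an earlier admission or qualifying drug change. An attempt leading to admission counts. A death falls under serious adverse event reporting, and a participant with no final lithium result is a primary-outcome failure.
- **That comparison across diagnoses is spoiled.** The trial compares arms, and diagnosis is a stratification factor. No comparison of exacerbation rates between diagnoses is planned.
- **That the error favours one arm.** Monitoring could plausibly change admissions for lithium toxicity, but the documents give nothing to establish this. The modelled error is equal in both arms and pulls the result toward no effect.

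It also stands that the outcome is secondary and exploratory, and that the article itself concedes too little power for it.

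**Conclusion.** The point holds as a defect in the definition of one secondary outcome. Followed as written, the rule can count unrelated or side-effect admissions as mood exacerbations. It can also miss a narrow class of real episodes, and a suicide with no earlier component. How often either would occur cannot be learned from the documents.

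The sizes shown rest wholly on assumed risks and equal error in both arms. On those assumptions the dilution is visible on the ratio scale (0.50 to 0.57-0.69) and modest on the difference scale (15.0 to 14.25-12.75 points). The primary outcome and its conclusion are unaffected. The change is still worth making, because this is the only measure of mood relapse and the repair is mostly wording.

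**What to change.** Before unmasking, amend the definition as follows:

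1. Count a hospitalization when the admitting department is psychiatry or the coded main diagnosis is a mood disorder. Both are objective and avoid a judgement of cause by treating physicians, who know the allocation.
2. Count antipsychotics, valproic acid, carbamazepine and lamotrigine when added or increased, as antidepressants already are.
3. Count death by suicide as an event.
4. Report all-cause hospitalization separately, and the composite as published alongside the revised one, so that readers can see what the change does.

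**Cost.** Data are to be extracted manually from the hospital record after trial completion, and the published rule already requires dose increases to be identified for lithium and antidepressants. No extra patient contact is needed. Suicide outside hospital may have to come from serious adverse event reports. Some increases counted under item 2 will not be for relapse, as is already true of antidepressants. With 101 patients recruited by 11 September 2019, the change needs approval from the university ethics committee and then the hospital's review board.
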